### Observation of intervention delivery

A total of eight semi-structured observations of intervention delivery by trained FN, that is, one per ICU, will be conducted to assess intervention fidelity and the establishment of structures for the FSI using a semi-structured fidelity audit observation tool. The tool bases on the intervention manual and was developed by the research team. It consists of four items on available structures for the FICUS study and 59 FSI activities corresponding to the three main components (1) engaging and liaising, (2) supporting and (3) communicating. Activities will be rated according to their performance by the FN (performed, partially performed, not performed, not applicable). In addition, the timepoint of the conversation (eg, admission) and the type of conversation (eg, on-site, via telephone) will be documented. An additional text box at the end of the tool will allow to document observations about the ICU context. The tool was pretested once by one researcher. All observations will be conducted by a doctoral student or a researcher, which are both trained in family systems nursing and are expected to last 2–4 hours each.

### Case conference

Monthly case conferences with FNs will be held as moderated group discussions to ensure quality of FSI delivery and to support consistency and adherence to the FSI activities. During case conferences, a specific family case will be presented by FN’s and FN’s will have the opportunity to discuss, to share their experiences and to reflect on the presented case. Based on the discussions, field notes will be taken by a doctoral student and FNs’ participation rate will be captured, as it is an indicator for fidelity receipt. Participation of the FN will be documented in a structured participation form. All case conferences will be held online by two senior researchers trained in family systems nursing and will last 60 min.

### Quantitative measures

#### Fidelity Self-Rating Tool

To capture quality and consistency of intervention performance (fidelity enactment), FN’s appraisal of self-perceived engagement and performance in FSI delivery will be assessed two times using the Fidelity Self-Rating Tool (Fidelity-SRT). The tool is based on the intervention manual and was developed by the FICUS research team. It includes three subscales according to the intervention components: (1) engaging and liaising (15 items), (2) supporting (27 items) and (3) communicating (15 items). All items will be rated on 5-point Likert scale (1=never to 5=always) regarding the last 3–5 families taken care of by the FN. A low mean score indicates low self-perceived success in FSI performance whereas a higher score means higher succeed in intervention delivery. The Fidelity-SRT was pretested by two KP and requires approximately 10 min to complete.

#### Intervention Capacity Assessment

To assess FN’s availability as defined per trial protocol to ensure provision of intervention capacity (fidelity delivery), the Intervention Capacity Assessment (ICA) will be completed once during process evaluation by KP’s. The ICA consists of two self-developed items referring to the 4 weeks prior to the assessment and include: (1) was there always at least one FN available to deliver the FSI during 5 days per week?; (2) (only for FN) to what extent was it possible to provide the FSI to family members according to the timeline requirements of the protocol and the needs of the family? Both items will be rated on a 5-point Likert scale ranging from 1 (never) to 5 (always).

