### Implementation outcomes

We will investigate the implementation outcomes of fidelity, feasibility, acceptability, appropriateness and sustainability.^39^ As fidelity is vital to evaluate our intervention and implementation theory for predicting effectiveness outcomes,^55 56^ we chose it as the primary outcome. Fidelity is defined according to the Conceptual Framework for Implementation Fidelity,^57 58^ and has been operationalised within the three domains of delivery, receipt and enactment as outlined by Bellg and colleagues.^59^

We will investigate feasibility, appropriateness and acceptability because these outcomes play a critical role in implementation research and serve as indicators of the effect of the implementation process and as prerequisites for achieving the desired service and family outcomes.^60^ To understand how the implementation develops over time and how to best support long-term delivery, we will investigate sustainability as well as post implementation sustainment outcomes.^61^

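### Item 2 of the Intervention Capacity Assessment puts protocol timeline and family needs under one rating, so a score below 5 cannot be traced to either

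*Protocol article*

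**What the plan says.** The section Implementation outcomes says of fidelity that "we chose it as the primary outcome" and that it is "operationalised within the three domains of delivery, receipt and enactment". Table 2 lists availability as one of four entries under delivery. Its sources are the ICA at T1 and focus group interviews at T4.

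The section Intervention Capacity Assessment gives the tool's purpose as assessing family nurses' "availability as defined per trial protocol to ensure provision of intervention capacity (fidelity delivery"). It describes the content as follows: "The ICA consists of two self-developed items referring to the 4 weeks prior to the assessment". The tool "will be completed once during process evaluation".

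- Item 1, for all key clinical partners: "was there always at least one FN available to deliver the FSI during 5 days per week".
- Item 2, for family nurses only: to what extent the intervention could be provided to family members "according to the timeline requirements of the protocol and the needs of the family".

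On the response format, the article says: "Both items will be rated on a 5-point Likert scale ranging from 1 (never) to 5 (always"). It describes no separate rating, follow-up question or scoring rule for the two halves of item 2.

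**The concern.** Item 2 is double-barrelled: it asks for one answer against two standards. The protocol's timeline is set in advance, while what a family needs varies from case to case. A nurse may serve a family well by departing from the timeline, or keep to the timeline and leave needs unmet. Only the timeline half can be read against a definition in the trial protocol, which is what the ICA is said to assess. The other half concerns fit to families.

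What is at stake is the interpretation of one of the two ICA items. The study compares eight ICUs as cases and wants to explain why implementation went well or badly. Low and middle ratings are the ones that call for explanation, and they are the ones this item leaves open. Two ICUs could also differ on it only because their nurses weigh the two halves differently.

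**Working it through.** The article states no sample size, power or error rate for this item, so there is no figure to reproduce. The check is whether one rating identifies the timeline part.

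**Inputs.** From the ICA section: two standards in item 2, and one rating on a scale of 1 to 5. How nurses combine the two standards is not stated, so two rules are assumed.

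Let T be the rating a nurse would give for the timeline alone, N the rating for family needs alone, and R the single rating recorded.

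**Rule A: the nurse reports the lower of the two, R = min(T, N).** This is the literal reading of a question that joins its conditions with *and*. Given R, T can be any value from R to 5:

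- R = 1: T from 1 to 5
- R = 2: T from 2 to 5
- R = 3: T from 3 to 5
- R = 4: T is 4 or 5
- R = 5: T is 5

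The rating is then only a lower bound for the timeline, and it fixes T only at 5.

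**Rule B: the nurse averages, R = (T + N)/2, taking the pairs whose average is a whole number.** Then N = 2R − T, and both T and N must lie between 1 and 5:

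- R = 1: T is 1
- R = 2: T from 1 to 3
- R = 3: T from 1 to 5, through the pairs (1,5), (2,4), (3,3), (4,2) and (5,1)
- R = 4: T from 3 to 5
- R = 5: T is 5

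**Reading the two together.** A rating of 5 gives T = 5 under both rules. A rating of 1 gives T = 1 if nurses average, but leaves T entirely open if they report the lower part. Ratings of 2, 3 and 4 leave T open under both rules. Since the rule in use is unknown, no rating below 5 can be attributed to the timeline or to family needs.

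**After a split.** With separate ratings T is recorded directly, so each answer gives one timeline value and no assumption about combination is needed.

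**What else covers this ground.** Item 1 asks only about the presence of a family nurse and does not share the fault. Table 2 takes relative frequency, absolute dose and consistency from the intervention fidelity logs at T1 to T4. The section Intervention Fidelity Logs does not name adherence to the timeline among the recorded characteristics, but its list is given as examples, so contact dates may be recorded.

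**The case against.** The strongest reply is that little depends on this item. Item 1 asks directly about family-nurse availability, by a single criterion and of all key clinical partners, so availability is still measured quantitatively if item 2 is set aside. Delivery itself is measured by the logs, which family nurses complete for each included trial participant. Item 2 asks what was possible, so even after a split it would give perceived capacity and not observed adherence. All of this stands, and it limits the point to one supplementary item.

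A second reply is that qualitative data will help interpret an ambiguous rating. Small group interviews at T1 and T3 ask about hindrances and about fit to families' needs, focus groups at T4 are a listed source for availability, and triangulation by case is planned. This softens the consequence but does not recover the timeline half of a rating already given.

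A third reply is that, read literally, a 5 means both standards were always met, and a 4 means the timeline was met at that level or better. The first part is accepted, and it is why the point concerns ratings below 5. The second part depends on every nurse reading the item that way.

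Finally, the supplement with detailed operationalisation and the full trial protocol are not shown. A different layout of the item there would change this reading.

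A reader might go further and infer that the study cannot tell whether delivery kept to protocol, or that the primary outcome is compromised. The documents do not support either, because item 2 is not the measure of delivery and fidelity has several other sources.

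**Conclusion.** The fault is real and stands in the printed wording: item 2 joins two standards under one rating, and a rating below 5 cannot be assigned to either. It affects one of two items in a tool given once, within one of four delivery entries of the primary outcome. It is a minor, localised measurement fault that is cheap to correct.

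No numerical size should be attached to it. A reader might want to express it as a shift in an ICU's mean score. The article does not say how often timeline and needs diverge, how many family nurses answer in each ICU, or that ICU means will be reported (the quantitative analysis section also allows medians or frequencies), so any such figure would rest on arbitrary choices. The two combination rules in the working are assumptions that show what a rating leaves open. They are not estimates of bias.

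The conclusion assumes that the item is administered as the article describes it.

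**What to change.** Split item 2 into two items with the same recall period and response scale:

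- 2a: to what extent the intervention could be provided on the protocol's timeline;
- 2b: to what extent it could be provided according to the family's needs.

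Use 2a, with item 1, for availability under fidelity of delivery, and report 2b separately. Describe 2a as perceived capacity and not as observed adherence.

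The article dates the study from June 2022 to January 2024, so the T1 assessment may already be complete. In that case, report item 2 as a composite of timeline and family needs and do not present it as timeline adherence. If the logs hold contact dates, derive timeline adherence from them.

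The cost is one extra short question for family nurses, with no added visit or analysis method. If the T1 data are already in, it is a sentence in the report and, where dates exist, a derivation from the logs.

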#### Intervention Fidelity Logs

FSI characteristics, such as duration in minutes, frequency, delivery mode, intervention activity (as defined in the intervention manual) will be recorded in a structured, online intervention log, which is part of the clinical trial electronic data capture system REDCap.^65^ The logs are completed by FN for each included trial participant on an ongoing basis.

#### Family Nursing Practice Scale

To assess FN’s appraisal of practice skills and their reflection in working with families, the 10-item German version of the ‘Family Nursing Practice Scale (FNPS)’ will be used.^66^ Items will be scored on a 5-point Likert-type scale ranging from 1 (high level) to 5 (low level). Lower mean scores will represent higher practice skills. The FNPS was validated in critical care, suggesting high internal consistency (Cronbach’s alpha 0.84).^66^

#### Feasibility Intervention Measure, Acceptability of Intervention Measure and Intervention Appropriateness Measure

To assess KPs’ perceived level of feasibility, acceptability and appropriateness of the FSI, adapted psychometrically validated German versions of the Feasibility Intervention Measure (FIM), Acceptability of Intervention Measure (AIM) and Intervention Appropriateness Measure (IAM) will be completed two times. Each of these surveys include four items that use a 5-point Likert scale ranging from 1 (completely disagree) to 5 (completely agree). A recurring adaption is made by inserting ‘FSI’ into the appropriate space on the instrument for example, ‘(insert Intervention) is doable’ will become ‘FSI is doable’. All three surveys are reliable and pragmatic instruments with a high Crohnbach’s alpha (FIM α=0.89; AIM α=0.80, IAM; α=0.87).^60 67^

#### Normalisation Measure Development questionnaire

To assess HP’s perceived level of integration, the German version of the Normalisation Measure Development (NoMAD) will be used two times.^68^ It includes 20 items using a 5-point Likert scale ranging from 1 (completely disagree) to 5 (completely agree) and is adaptable by specifying the ‘(the intervention)’ to study purpose,^69^ that is, the ‘FSI’. The NoMAD instrument has high face validity, construct validity and internal consistency for assessing perceptions of factors relevant to the integration of the FSI. Internal consistency (Cronbach’s alpha) was reported as follows: coherence (four items, α=0.71); collective action (seven items, α=0.78); cognitive participation (four items, α=0.81) and reflexive monitoring (five items, α=0.65). Overall, the normalisation scale was described as highly reliable (20 items, α=0.89).^69^

### Sustainability implementation survey

To assess both, KP’s appraisal of sustainability determinants and post implementation sustainment outcomes, a self-developed sustainability survey will be sent at 6 and 12 months after the last intervention delivery and before the follow-up completion by the last study participant. The survey will include questions about the extent to which the FSI is still delivered as intended after FICUS study support is terminated (sustainability) and continued enactment of processes and practices in daily ICU routine that have been conveyed and learnt through the FSI.^70^ All items will be rated on a 5-point Likert scale ranging from 1 (completely disagree) to 5 (completely agree).

### Demographics

Information on participants’ age, gender, profession, institution, level of employment, level of education, work experience in the ICU, overall work experience in the profession and whether family nursing was part of the curriculum of their training and/or studies, will be collected. Furthermore, cluster data at ICU level will be collected to describe the eight cases in detail. Cluster data will include ICU cluster size (number of HP), number of beds, number of admissions per year and average length of stay.

All surveys will be implemented in UNIPARK software.

### Data analysis

#### Qualitative data analysis

Data analysis of the process evaluation will require prompt analysis of interview data to rapidly develop or modify implementation strategies in case of need. Hence, small group interviews will be analysed using an adapted approach of Rapid Identification of Themes from Audio recordings,^71^ in combination with a deductive approach guided by NPT.^47^ This form of directed content analysis will apply the following steps: (1) specifying the evaluation foci, (2) identifying themes from audio recordings, (3) creating a codebook, (4) coding and refining the codebook and (5) sorting codes into themes inductively and deductively drawing on NPT constructs.^72^

Qualitative data from the summative evaluation (T4) will be analysed using content analysis, which allows the use of deductive and inductive strategies. It uses the following steps: (1) reading each of the transcribed interviews to get familiar with the data, taking notes of first impressions to gain a sense of the whole phenomenon, (2) identifying and developing codes for each unit of meaning, (3) developing of definitions for each code and group them into categories of related meanings and (4) synthesising codes and categories into themes.^72 73^

#### Quantitative data analysis

Raw data will be verified, encrypted and entered into R Project for analysis. Descriptive statistics will be computed for the entire sample, by case and by data collection timepoint. Depending on scale level and distribution, results will be presented either as absolute and relative frequencies, as mean and SD, or as median and IQR. If scale levels and distributions allow, differences in central tendency will be tested by Student’s t-test (paired or unpaired), with Welch’s correction in the case of variance heterogeneity (unpaired case). Otherwise, differences in the distribution of ordinal data will be tested by Wilcoxon’s signed-rank test (paired case within the same clusters or individuals over two timepoints, eg, Fidelity-SRT or NoMAD; unpaired case between clusters or individuals, eg, FNPS at baseline, referred to as Mann-Whitney U test). For nominal comparisons between clusters or individuals (unpaired), a χ^2^ test will be used if observed and expected frequencies allow for it, and Fisher’s exact test will be used otherwise. For nominal comparisons within clusters or individuals over different timepoints (paired), McNemar’s test will be used (or Cochran’s Q test if a binary attribute is compared over more than two matched observations).^74^

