**Methods and analysis:**

This mixed-methods multiple case study is guided by two implementation theories, the Normalisation Process Theory and the Consolidated Framework for Implementation Research. Participants are key clinical partners and healthcare professionals of eight ICUs allocated to the intervention group of the FICUS trial in the German-speaking part of Switzerland. Data will be collected at four timepoints over the 18-month active implementation and delivery phase using qualitative (small group interviews, observation, focus group interviews) and quantitative data collection methods (surveys, logs). Descriptive statistics and parametric and non-parametric tests will be used according to data distribution to analyse within and between cluster differences, similarities and factors associated with fidelity and the level of integration over time. Qualitative data will be analysed using a pragmatic rapid analysis approach and content analysis.

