### Setting

The FSI will be implemented in eight of sixteen ICUs participating in the FICUS trial, which have been randomly assigned to the intervention arm.^4^ All ICUs are certified by the Swiss Society for Intensive Medicine; two are situated in a university affiliated, and six in a cantonal or teaching hospital.

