### Participants and sampling

Data will be collected from KP and HP by a doctoral student and a senior researcher. The senior researcher is trained and skilled in qualitative data collection and will train and supervise the doctoral student in doing so. KP are local clinical and management staff involved in the implementation and delivery of the FSI (n=45) and will include local implementers (LI) who support the implementation process, trained family nurses (FN), who are registered nurses with a certification in ICU nursing or equivalent, who are trained in family systems nursing and deliver the FSI, as well as a nurse and physician team leaders and/or their deputy. Quantitative and qualitative data will be gathered from all KP during the process evaluation.

The second participant group will include HP working on the participating ICUs (approximately n≈750). Quantitative data for the summative evaluation will be gathered from all HP with an anticipated response rate of 50%–70% using a comprehensive sampling strategy. To increase response rates, 3-weekly reminder emails will be sent twice. Qualitative data will be gathered from a subsample of HP (n=80–100) using a purposive sampling strategy. Inclusion criteria will be: ICU physicians or nurses working clinically on study units, having an active or influential role in the implementation/delivery of the FSI and/or having either knowledge/experience with the FSI and/or a clinical leadership responsibility, having worked at the ICU for at least 6 months.

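### The named tests may be run on ICUs or on individuals, with no rule for the unit and no method for nesting in eight ICUs, so ICU-level factors tested on individual records have inflated type I error

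*Protocol article*

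**What the plan says.** The Quantitative data analysis section of the protocol article names Student's or Welch's t-test, Wilcoxon's signed-rank test, the Mann-Whitney U test, the chi-square or Fisher test, and McNemar's or Cochran's Q test. The ordinal and nominal tests, paired and unpaired, are each described as applying to clusters or to individuals. The unpaired ordinal test, for example, is given as "unpaired case between clusters or individuals, eg, FNPS at baseline, referred to as Mann-Whitney U test". The section contains no mixed model, generalised estimating equation, cluster-robust variance or ICC, and no step that aggregates answers to ICU level.

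The Abstract says what the tests are for: "within and between cluster differences, similarities and factors associated with fidelity and the level of integration over time". Under Setting, "The FSI will be implemented in eight of sixteen ICUs participating in the FICUS trial". Under Participants and sampling, "Quantitative data for the summative evaluation will be gathered from all HP", where HP are the healthcare professionals of those ICUs. Results are to be summarised as frequencies, mean and SD, or median and IQR. Confidence intervals are not mentioned.

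**The concern.** Feasibility, acceptability and integration of a unit-wide intervention are partly properties of the unit, so colleagues in one ICU will tend to answer alike. A test that counts each respondent as independent then underestimates the variance of any contrast that runs along ICU lines. The same holds for an overall change over time if the change itself differs between ICUs.

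The second research question asks which contextual determinants influence integration and explain its effect on outcomes. ICU size, beds, admissions and length of stay are collected. An analyst who relates such a characteristic to several hundred individual answers would be following the protocol, and could report ordinary variation between ICUs as a determinant. The article intends its findings to inform recommendations for scale-up, so a false determinant would carry forward.

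**Working it through.** **Inputs from the protocol article.** Eight ICUs (Setting). Healthcare professionals (Participants and sampling): "The second participant group will include HP working on the participating ICUs (approximately n≈750", with an "anticipated response rate of 50%–70% using a comprehensive sampling strategy". Key clinical partners, including the family nurses: "involved in the implementation and delivery of the FSI (n=45".

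**Assumptions not in the article.** Two-sided 5% level, ICC from 0.01 to 0.10, equal ICU sizes, and normal data in the simulation. The article states no significance level, power, ICC or effect size, so it has no figure to reproduce.

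**Step 1: respondents per ICU (m).**
- All staff: 750 × 0.50 = 375, and 375 / 8 = 46.9; 750 × 0.70 = 525, and 525 / 8 = 65.6.
- Key partners: 45 / 8 = 5.6. Family nurses are a subset, so nurse-only scales have fewer.

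**Step 2: design effect for an ICU-level factor.** DE = 1 + (m − 1) × ICC. At ICC 0.05 this is 1 + 45.875 × 0.05 = 3.29 and 1 + 64.625 × 0.05 = 4.23 for all staff, and 1 + 4.625 × 0.05 = 1.23 for key partners.

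**Step 3: true level of a nominal 5% test on individuals.** Approximately 2 × [1 − Φ(1.96 / √DE)]. For DE = 3.29, √DE = 1.81, 1.96 / 1.81 = 1.08, and the level is 28%.

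| Assumed ICC | All staff: DE | All staff: level by formula | All staff: Welch test, simulated | Key partners: DE | Key partners: level by formula |
|---|---|---|---|---|---|
| 0.01 | 1.46-1.65 | 10.5-12.7% | 10-13% | 1.05 | 5.5% |
| 0.02 | 1.92-2.29 | 15.7-19.6% | 16-20% | 1.09 | 6.1% |
| 0.05 | 3.29-4.23 | 28.0-34.1% | 28-35% | 1.23 | 7.7% |
| 0.10 | 5.59-7.46 | 40.7-47.3% | 41-49% | 1.46 | 10.5% |

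The simulation used eight ICUs with 47 or 66 respondents each, split 2 v 6 or 4 v 4, with 10,000 datasets per setting. The Mann-Whitney test (1,500 datasets per setting) gave 9.4-13.2%, 15.0-19.7%, 26.9-34.4% and 39.3-47.5% at the four ICCs. With 6 respondents per ICU, the simulated Welch level at ICC 0.10 was 10.9-11.4%.

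**Step 4: pooled change over time.** A paired test on individuals behaves the same way when the change varies by ICU. Reading the ICC as the share of the variance of change that lies between ICUs, the simulated level with 47 or 66 per ICU was 10.4-12.9%, 15.8-19.4%, 28.5-34.3% and 40.7-48.2%. These figures need healthcare professionals to answer twice. The section on the normalisation questionnaire (NoMAD) says they do, whereas the Study overview involves them only at T4. If only key partners answer twice, their smaller inflation applies.

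**Step 5: where there is no inflation.** A factor split evenly within each ICU gave 3.8-5.2% when clustering was ignored. A comparison of two named ICUs concerns those two units as they are, and clustering does not invalidate it.

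**Step 6: ICUs as the unit.** A two-sample t-test on the eight ICU means gave 4.5-5.6% at every ICC from 0 to 0.10. An exact rank test on eight ICUs has a floor. The smallest two-sided p-value is 2 / C(8,2) = 2/28 = 0.071 for 2 v 6, 2 / C(8,4) = 2/70 = 0.029 for 4 v 4, and 2 / 2⁸ = 0.008 for a signed-rank test.

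**The case against.** The text says clusters or individuals, so a test on ICU summaries is already allowed. A reader might infer that the plan fixes the individual as the unit and that all its p-values are wrong. The wording does not support that. It does, however, treat the two units as interchangeable and gives no aggregation step. Two details point towards individuals. The unpaired example is a scale scored by single family nurses. The chi-square test is the first choice for unpaired nominal data, yet eight ICUs in a 2 × 2 table average two per cell, below the conventional expected count of 5.

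Other limits stand in full:
- A reader might infer that intervals will be too narrow, but the article plans none.
- A reader might carry the large figures over to fidelity, the primary outcome. The Family Nursing Practice Scale and the Fidelity Self-Rating Tool are answered by family nurses, where the inflation is mild. The intervention logs are not named in the analysis section, so their testing entry by entry is an inference.
- No test of university-affiliated against other ICUs is planned. The Setting section only describes the units ("two are situated in a university affiliated, and six in a cantonal or teaching hospital"), and the 2 v 6 split serves here as an illustration. Table 2 assesses contextual determinants by interview, and cross-case synthesis addresses both research questions. The Abstract nevertheless assigns tests to factors associated with fidelity and integration, without limiting these to factors that vary within ICUs.
- This is a multiple case study reported in a condensed article, and an analysis plan not shown may settle the unit. Random-effects structure and degrees of freedom can properly be left to it. The tests and their permitted units are stated here, though, and one permitted use does not hold its level.

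**Conclusion.** The concern holds in a limited form. The stated methods permit an analysis that does not hold its nominal level. This affects ICU-level factors, and pooled changes that vary by ICU, when they are tested on individual records.

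For the all-staff survey the error is at least about double the nominal 5% at an ICC of 0.01 and roughly six to seven times it at 0.05. For scales answered by key partners or family nurses it stays at about 5.5-10.5%. The size depends on the ICC, which the article does not give, and on the assumed 5% level and equal ICU sizes. That clustered data need a method or a stated unit does not depend on these assumptions. A study designed to find differences between ICUs cannot plausibly assume an ICC of zero.

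**What to change.** In the Quantitative data analysis section, state the unit for each kind of comparison:

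1. **ICU-level factors:** test only on the eight ICU summaries, noting that an exact 2 v 6 rank test cannot go below p = 0.071, or label these p-values as descriptive.
2. **Individual-level factors:** use a linear mixed model with an ICU random intercept and a small-sample degrees-of-freedom correction. If log entries are tested, add nurse and family levels.
3. **Pooled changes over time:** use the same model on the change scores, so that the ICU random intercept captures changes that differ between ICUs. A random intercept on the raw scores alone would not.
4. **Comparisons of named ICUs:** keep the present tests, and say that the ICUs are treated as fixed cases.
5. Report the ICC for each scale in the all-staff survey.

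No new data are needed. The cost is slightly more analysis work, larger p-values and few ICU-level factors that eight units can test.
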